## 4.0 TREATMENT PLAN

### 4.1 Treatment Dosage and Administration

- 4.1.1 This phase I clinical trial will begin with hemilarynx CyberKnife radiotherapy to a dose of 50 Gy delivered in 15 fractions. If this dose/fraction scheme has no dose limiting toxicity, there will be a reduction to 10 fractions to a bio-equivalent dose of 45 Gy. If this dose level is tolerated without dose limiting toxicity, there will be an additional reduction to 5 fractions to a bio-equivalent dose of 42.5 Gy. The patients will also be followed prospectively for voice quality and quality of life. The dose will be prescribed to provide at least 95% planning treatment volume (PTV) coverage.

| Agent         | Pre-medications;
Precautions                                                             | Dose | Route | Schedule                                |
|---------------|---------------------------------------------------------------------------------------------|------|-------|-----------------------------------------|
| Dexamethasone | Pre-medicate with Dexamethasone 1 hour prior to radiation treatments for dose level 1 and 2 | 4 mg | Oral  | Daily 1 hour prior to radiation therapy |

| Dose-Escalation Schedule |                                                                                     |                            |
|--------------------------|-------------------------------------------------------------------------------------|----------------------------|
| Dose Level               | Dose of the Study Agent(s)*                                                         | Minimum Number of Patients |
| Level -1                 | 52.5 Gy in 16 fractions of 3.28 Gy per fraction daily                               | 3                          |
| Level 0                  | 50 Gy in 15 fractions of 3.33 Gy per fraction daily, delivered 5 fractions per week | 3                          |
| Level 1                  | 45 Gy in 10 fractions of 4.5 Gy per fraction daily, delivered 3 fractions per week  | 7                          |
| Level 2                  | 42.5 Gy in 5 fractions of 8.5 Gy per fraction daily, delivered 2 fractions per week | 7                          |

| Toxicity Dose Reductions                                                                                    |                                                               |

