| Grade 5 Death                                                                                                                          | Termination of trial with reporting of dose limiting toxicity |
| Hypoparathyroidism                                                                                                              |                                                               |
| Grade 1 Asymptomatic; clinical or diagnostic observations only; intervention not indicated                                             | None                                                          |
| Grade 2 Moderate symptoms; medical intervention indicated                                                                              | None                                                          |
| Grade 3 Severe symptoms; medical intervention or hospitalization indicated                                                             | See Section 10 Statistical Considerations                     |
| Grade 4 Life-threatening consequences; urgent intervention indicated                                                                   | Termination of trial with reporting of dose limiting toxicity |
| Grade 5 Death                                                                                                                          | Termination of trial with reporting of dose limiting toxicity |

Dose limiting toxicities (DLT) will be defined as occurring whenever any one of the following are manifested as occurring whenever any one of the following are manifested: laryngeal edema (grade 4 or 5), dyspnea (grade 4 or 5), stridor (grade 4 or 5) probably or definitely related to the protocol.

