#### **4.10 Duration of Therapy**

The end of protocol therapy will occur if:

- Inter-current illness that prevents further administration of treatment
- Unacceptable adverse event(s)
- Subject decides to withdraw from the study, or
- General or specific changes in the patient's condition render the subject ineligible for further treatment at the discretion of the investigator or treating physician

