#### **4.12 Removal of Subjects from Protocol Therapy**

Subjects will be removed from therapy if dose limiting toxicity is experienced. The Principal Investigator will be notified, and reason documented for study removal and the date the subject was removed in the Case Report Form. The subject should be followed-up per protocol.

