## 5.5 Removal of Subjects from Study

Subjects can be taken off the study treatment and/or study at any time at their own request, or they may be withdrawn at the discretion of the investigator for safety, behavioral or administrative reasons. The reason(s) for discontinuation will be documented and may include:

- 
- 5.5.1 Subject voluntarily withdraws from treatment (follow-up permitted);
  - 5.5.2 Subject withdraws consent (termination of treatment and follow-up);
  - 5.5.3 Subject is unable to comply with protocol requirements;
  - 5.5.4 Subject demonstrates disease progression (unless continued treatment with study drug is deemed appropriate at the discretion of the investigator);
  - 5.5.5 Subject experiences toxicity that makes continuation in the protocol unsafe
  - 5.5.6 Treating physician judges continuation on the study would not be in the subject's best interest;
  - 5.5.7 Subject becomes pregnant (pregnancy to be reported along same timelines as a serious adverse event);
  - 5.5.8 Development of second malignancy (except for basal cell carcinoma or squamous cell carcinoma of the skin) that requires treatment, which would interfere with this study
  - 5.5.9 If a research subject cannot be located to document survival after a period of 2 years, the subject may be considered "lost to follow-up." All attempts to contact the subject during the two years must be documented and approved by the Data Monitoring Committee.

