## **10.0 Statistical Considerations**

### **10.1 Primary endpoint**

The primary endpoint of this phase I clinical trial will be to either reach the minimum number of fractions that is tolerated for larynx irradiation or a dose of 42.5 Gy in 5 fractions whichever comes first. Patients will be treated in cohorts of 3-15. Toxicity will be graded using the National Cancer Institute (NCI) Common Toxicity Criteria for Adverse Events (CTCAE) version 4.0. A dose-limiting toxicity (DLT) is a grade 3 or greater toxicity definitely related to treatment in the following categories: laryngeal edema, voice, dyspnea, stridor, or cough. All reported DLTs will be verified by the study

chair, data monitoring committee, and as appropriate, independent review before final determination that a DLT has in fact occurred. The number of fractions will be reduced from 15, to 10 fractions, and then to 5 fractions (reduced by 5 fractions per step). The phase 1 portion of the study will be completed with either of the following events occur: 1) the MTD for a cohort is reached or 2) when the lowest number of fractions is treated and tolerated (42.5 Gy in 5 fractions).

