## 10.2 Phase 1 waiting periods

Fraction reduction for this phase 1 clinical trial will not occur until sufficient waiting has occurred after a cohort has been treated. A period of 90 days must pass before further fraction reduction for the purpose of assessing toxicity. If 90 days have passed without a DLT at a dose level, the trial will be allowed to the next level, so long as either criteria for defining the MTD or criteria for further fraction reduction is not reached. If the maximum number of patients are enrolled to a given fraction level, yet criteria for follow-up is not reached in a representative sample of patients, further enrollment to the protocol will be suspended until adequate follow-up is reached. No action will be taken for Grade 1 or Grade 2 toxicities. If any 2 Grade 3 toxicities occur within a dose level likely or definitely related to radiation therapy, the trial will be terminated with reporting of DLT at that dose level. Any Grade 4 or Grade 5 toxicity found to be likely or definitely related to treatment will result in termination of the trial with reporting of DLT at that dose level.

Grade 3 toxicities likely or definitely related to protocol therapy will result in action in schema provided below:

[figure not shown]

For level -1, if a Grade 3 toxicity occurs, the trial will be terminated with reporting of DLT.

For level 0, if a Grade 3 toxicity occurs, a step de-escalation will occur to level -1. If no grade 3 toxicities are experienced at level 0, the trial will proceed to level 1.

---

For level 1, if there are no Grade 3 toxicities after initial enrollment of 7 patients, an additional 8 patients will be enrolled. If there is no grade 3 toxicity after enrollment of an additional 8 patients, the trial will proceed to level 2. If there is a 1 grade 3 toxicity in the additional 8 patients, the trial will proceed to level 2 at the discretion of the PI and DSMC.

For level 1, if there is 1 Grade 3 in the initial 7 patient cohort, an additional 8 patients will be enrolled. If there is an additional Grade 3 toxicity at this level, the trial will be terminated with reporting of DLT. If there are no further grade 3 toxicities in the additional 8 patients, proceeding to the next level will be done at discretion of the DSMC and PI.

For level 1, if there are 2 grade 3 toxicities in the initial 7 patient cohort, the trial will be terminated with reporting of DLT.

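### Sections 4.1 and 10.1 define dose-limiting toxicity incompatibly, which leaves patient removal under 4.12 and the reporting of DLTs unsettled

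*Protocol*

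**What the plan says.** Two definitions stand in the current protocol text.

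- Section 4.1, after the toxicity table: "laryngeal edema (grade 4 or 5), dyspnea (grade 4 or 5), stridor (grade 4 or 5) probably or definitely related to the protocol".
- Section 10.1: "a grade 3 or greater toxicity definitely related to treatment in the following categories: laryngeal edema, voice, dyspnea, stridor, or cough".

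The term is then used in these places:

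- Section 4.12: "Subjects will be removed from therapy if dose limiting toxicity is experienced". There is no discretion in that sentence.
- Section 4.1.1, on moving from level 1 to level 2: "If this dose level is tolerated without dose limiting toxicity, there will be an additional reduction to 5 fractions".
- Section 10.1 has every reported DLT verified by the study "chair, data monitoring committee, and as appropriate, independent review before final determination that a DLT has in fact occurred", without saying which definition is applied.
- Section 10.2 has a 90-day sentence that allows the next level if no DLT has occurred, subject to its own proviso about the criteria for MTD and fraction reduction. It also ends the trial, with a DLT reported, after two related grade 3 events in a level or after any one related grade 4 or 5 event.
- Section 4.13 treats three or more radiation treatments missed because of toxicity as a DLT. Neither definition includes this.

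Section 10.2 states its rules by level in grades, not in DLTs. For level 1, for example, the branch for "1 grade 3 toxicity in the additional 8 patients, the trial will proceed to level 2 at the discretion of the PI and DSMC". The toxicity table in 4.1 refers grade 3 events in all ten of its categories to Section 10.

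**The concern.** A phase I trial needs a single DLT definition that investigators can apply while a patient is on treatment. Here the two definitions differ in grade threshold, in categories and in attribution, and they cross: each counts events that the other does not. Because DLT definitions are applied during treatment, this is not something a later analysis plan can settle.

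The main stake is the individual patient. Two investigators who both follow the protocol could act differently on the same mid-course grade 3 event, one removing the patient from protocol radiotherapy and the other continuing. The second stake is the record: the trial could end with a DLT reported although one of the definitions, or both, says that none occurred.

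**Working it through.** **1. The plan's own figure.** The schema gives 17 to 48 patients. The level sizes reproduce this: minimum 3 + 7 + 7 = 17 (levels 0, 1, 2) and maximum 3 + 15 + 15 + 15 = 48 (levels −1, 0, 1, 2). Neither number depends on the DLT definition.

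**2. The definitions side by side.**

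| | Section 4.1 | Section 10.1 |
|---|---|---|
| Grade | 4 or 5 | 3 or higher |
| Categories | edema, dyspnea, stridor | the same three, plus voice and cough |
| Attribution | probably or definitely | definitely only |

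**3. How far they disagree.** Take the five 10.1 categories, the grades from 3 upwards that the 4.1 table lists, and two attributions (probable, definite). Edema, dyspnea and stridor have grades 3 to 5; voice and cough stop at grade 3.

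- All types: 3 × 3 × 2 + 2 × 1 × 2 = 22.
- DLT under 4.1 only: 3 categories × 2 grades × probable = 6.
- DLT under 10.1 only: 5 categories × grade 3 × definite = 5.
- DLT under both: 3 × 2 × definite = 6.
- DLT under neither: 5 × grade 3 × probable = 5.
- Check: 6 + 5 + 6 + 5 = 22. Discordant: 6 + 5 = 11.

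Reading *likely* in 10.2 as *probable*, the six types that only 4.1 counts end the trial under 10.2 in any case. For the conduct of the trial they differ in label only. That leaves five that can change an action: definite grade 3 edema, voice, dyspnea, stridor and cough.

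**4. Where those five matter.**

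- *Section 4.12.* Under 10.1 the event is a DLT and removal is required. Under 4.1 it is not, and stopping rests on judgement: unacceptable adverse events in 4.10, or in 5.5 "Subject experiences toxicity that makes continuation in the protocol unsafe". As a scale for what is at issue, one fraction is 3.33/50 = 6.7% of the prescribed dose at level 0, 4.5/45 = 10% at level 1 and 8.5/42.5 = 20% at level 2. Removal after fraction 3 of 5 at level 2, for instance, leaves 2 × 8.5 = 17 Gy of 42.5 Gy not given on protocol.
- *One definite grade 3 event in 15 at level 1.* Under 4.1 there has been no DLT, so 4.1.1 reads as automatic reduction to 5 fractions. Under 10.1 the 4.1.1 condition is not met. Section 10.2 gives the decision to the PI and DSMC, whether the event fell in the first 7 patients or the next 8.

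**5. Where the label is unclear.** Three outcomes make 10.2 end the trial with a DLT reported.

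| Outcome | DLT under 4.1? | DLT under 10.1? |
|---|---|---|
| Two definite grade 3 events in the five categories | no | yes |
| Two grade 3 events that are only likely related | no | no |
| One likely-related grade 4–5 airway event | yes | no |

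The 4.1 table and 10.2 also end the trial for a grade 4–5 event in the other table categories, such as myelitis or carotid injury. Neither definition covers these.

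**The case against.** The strongest reply is that trial conduct is settled elsewhere. The 4.1 table hands grade 3 events to Section 10, and 10.2 fixes de-escalation, expansion, advance and termination by grade counts that use neither definition. This largely stands: the conflict does not reach most cohort decisions.

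A reader might go further and infer that one grade 3 event in 15 produces contradictory instructions, and then put a probability on it. The documents do not support that. Section 4.1.1 says what follows if there is no DLT; it does not say that advance is allowed only then. The one-in-15 outcome has an explicit rule in 10.2, so its probability is not the probability of a changed decision. What remains is that, under the 4.1 definition, 4.1.1 sounds automatic where 10.2 is discretionary.

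A reader might also take the DLT count as the trial's main result and contrast the proportions under each definition. Section 10.1 makes the primary endpoint the smallest tolerated number of fractions, or reaching 42.5 Gy in 5. No DLT proportion or interval is specified, so that contrast would rest on an estimand the protocol does not state.

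On 4.12, it is fair to say that removal is from *protocol* therapy, that nothing shown forbids completing radiotherapy off protocol, and that a DLT must be verified before it is final. This limits the 17 Gy example to an illustration. It does not remove the conflict, since 4.12 still requires removal under one definition and not under the other. Finally, the 10.2 action schema is not visible here. It is introduced as a set of actions for grade 3 events, so it is unlikely to rank the definitions, but this could not be checked.

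**Conclusion.** The contradiction is real, and it should be fixed. Its practical reach is narrow: one clear difference in action (removal under 4.12 for a definite grade 3 event in the five 10.1 categories), uncertainty over which events are verified and reported as DLTs, and one place where 4.1.1 reads more strongly than the 10.2 rule. The count of 11 discordant types in 22, with 5 that can change an action, describes how the definitions overlap. It is not a measure of frequency, because the protocol gives no rate of grade 3 events.

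The conclusion assumes that *likely* in 10.2 means *probable* on the Section 4.7 scale, and that the schema not shown does not rank the two definitions. It does not support a claim that escalation decisions in general, or the primary endpoint, turn on which definition is used.

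**What to change.** Delete the DLT sentence in 4.1 and keep one definition, in 10.1, that matches the 10.2 action rules:

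- related grade 3 or higher events in the categories that 10.2 is meant to count (its text names none at present);
- any related grade 4 or 5 toxicity;
- one attribution threshold on the 4.7 scale, for instance *probable or definite*, replacing *likely* in 10.2;
- the 4.13 criterion of three or more treatments missed because of toxicity.

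State that the 10.2 counts govern advance, de-escalation and termination, and that neither the no-DLT condition in 4.1.1 nor the 90-day sentence overrides them. State in 4.12 whether a single grade 3 event ends protocol radiotherapy.

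Three of these are clinical decisions for the study team to confirm: the attribution threshold (10.1 now requires a definite relation), the category list (including grade 3 myelitis, skin, carotid, thyroid and parathyroid events, and the extension to any grade 4–5 toxicity), and the 4.12 rule. If the category list is left open, the mismatch with DLT reporting in 10.2 remains.

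The cost is a text amendment to 4.1, 4.12, 10.1 and 10.2. It needs no extra patients or assessments. Any events already recorded would be reclassified under the single definition.

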#### 4.2 CT-based simulation

For CyberKnife planning, a 4-D respiratory CT-scan will be performed for target delineation and generation of GTV and internal target volume (ITV). Intravenous contrast is recommended to be administered at time of CT-simulation. During simulation, an Aquaplast mask will be custom molded for daily immobilization during radiation treatments. A head rest will be positioned beneath the patient's head and neck fitted at discretion of treating physician that will position the neck in a slightly extended position that may be reproduced daily.

### 4.3 Target Volumes

#### Carcinoma *in situ* or cT1 lesions

The gross tumor volume (GTV) and internal target volume (ITV) will be contoured based upon 4-D respiratory gated CT-scan. The clinical target volume (CTV) will include the ITV plus a 2 mm geometric expansion that may be clinically modified at the discretion of the treating physician. For lesions coming within 2 mm of or involving the ipsilateral arytenoid, the arytenoid will be included in the CTV. For lesions located within 2 mm of the anterior commissure or involving the anterior commissure, the CTV will include the anterior commissure as well as 2 mm of the adjacent contralateral vocal cord. The planning treatment volume (PTV) will be the CTV plus a 3 mm uniform expansion in all directions.

#### cT2 lesions

The gross tumor volume (GTV) and internal target volume (ITV) will be contoured based upon 4-D respiratory gated CT-scan. The clinical target volume (CTV) will include the ITV plus a 2 mm geometric expansion that may be modified at the discretion of the treating physician, entire ipsilateral vocal cord, and ipsilateral paraglottic space. For lesions coming within 2 mm of or involving the ipsilateral arytenoid, the arytenoid will be included in the CTV. For lesions located within 2 mm of the anterior commissure or involving the anterior commissure, the CTV will include the anterior commissure as well as 2 mm of the adjacent contralateral vocal cord. The PTV will be the CTV plus a 3 mm uniform expansion in all directions.

#### Bilateral cord involvement

For lesions involving bilateral vocal cords, the clinical target volume (CTV) will include the ITV with 2 mm geometric margin that may be modified at the discretion of the treating physician, bilateral vocal cords, and bilateral paraglottic spaces. The arytenoids and/or anterior commissure will only be included in the CTV if the tumor involves or comes within 2 mm of it. The PTV will be the CTV plus a 3 mm uniform expansion in all directions.

### 4.4 Critical Structures

The following critical structures will be contoured as OAR.

- Right carotid artery – The right carotid artery will be identified and contoured from the level of the hyoid superiorly to the level of the cricoid inferiorly
- Left carotid artery - The right carotid artery will be identified and contoured from the level of the hyoid superiorly to the level of the cricoid inferiorly
- Thyroid gland - The thyroid is easily visible on a non-contrast CT due to its preferential absorption of Iodine, rendering it “brighter” or denser than the surrounding neck soft tissues. The left and right lobes of the thyroid are somewhat triangular in shape, and often do not converge anteriorly at mid-line. All “bright” thyroid tissue should be contoured.
- Anterior commissure – The anterior commissure will be defined as the 1 mm laterally along the true vocal cords from the midline of the anterior cords, and will be contoured unless gross tumor involves it or comes within 2 mm of it
- Ipsilateral arytenoid – The ipsilateral arytenoid of the laryngeal skeleton will be identified and contoured unless gross tumor involves or comes within 2 mm of it
- Contralateral Arytenoid – The contralateral arytenoid of the laryngeal skeleton will be identified and contoured
- Contralateral vocal cord – Unless there is bilateral vocal cord involvement, the contralateral true vocal cord will be identified and contoured

- Larynx – The entire laryngeal skeleton will be contoured including the thyroid cartilage, epiglottis, cricoids, and cuneiform cartilages.
- Spinal cord – The spinal cord will be contoured from 2 cm superior to 2 cm inferior from the larynx
- Skin – The skin will be contoured based upon an external contour of the body

#### 4.5 Dose Constraints

| OAR           | Volume | Dose          |
|----------------------|---------------|----------------------|
| Thyroid              | Mean          | <10% prescribed dose |
| Right carotid artery | Maximum point | <10% prescribed dose |
| Left carotid artery  | Maximum point | <10% prescribed dose |
| Spinal cord          | Maximum point | <5% prescribed dose  |
| Skin                 | Maximum point | <10% prescribed dose |

